## Abstract

**Background:**

IMPROVE aims to conduct a hybrid type 3 evaluation design to test the effectiveness of bundled implementation strategies on intervention fidelity of the Healthy School Start (HSS) program, while simultaneously monitoring effects on health outcomes of children and parents. The HSS is a 4-component family support program for children starting school (5–7 years of age) promoting healthy dietary habits and physical activity in the home environment to prevent childhood obesity and parents’ risk of developing type 2 diabetes.

**Methods:**

IMPROVE is a cluster-randomized controlled trial with two arms to evaluate and compare the effects of two different bundles of implementation strategies on intervention fidelity expressed as adherence and responsiveness at 12 and 24 months (primary outcomes). Thirty schools in two municipalities will participate in the study reaching about 1400 families per school year. In stakeholder workshops, key implementation determinants were identified according to the domains of the Consolidated Framework for Implementation Research. Through a consensus process with stakeholders, two bundles of implementation strategies were tailored to address context-specific determinants. Schools randomly assigned to group 1 will receive bundle 1 (Basic) and group 2 will receive bundle 1 + 2 (Enhanced). Bundle 2 consists of external facilitation, fidelity monitoring and feedback strategies. Secondary outcomes will include change in acceptability, appropriateness, feasibility, and organisational readiness as perceived by school staff. In addition, child weight status and diet, and parents’ feeding practices and risk of type 2 diabetes will be monitored. Linear and ordinal regression analysis will be used to test the effect on the primary and secondary outcomes, taking clustering and covariates into consideration where needed. Process evaluation will be conducted through key stakeholder interviews to investigate experiences of the program and perceptions on sustainability.

**Discussion:**

This systematic approach to investigating the effectiveness of two different bundles of implementation strategies tailored to context-specific determinants on the fidelity of the HSS intervention will provide new insight into feasible implementation strategies and external support needed for the HSS to be effective and sustainable. Results will help inform how to bridge the gap between the research on school-based health programs and routine practice in schools.

**Trial registration:**

Registered prospectively at ClinicalTrials.gov ID: NCT04984421, registered July 30, 2021

**Supplementary Information:**

The online version contains supplementary material available at 10.1186/s12889-021-11663-2.

## Contributions to the literature

Comparing the effectiveness of two bundles of implementation strategies tailored to context specific determinants identified by stakeholdersAdds to the knowledge on hybrid design studies in implementation researchAdds new perspectives on the construction of a fidelity score in a complex interventionAdds knowledge on the form and function for external facilitation support in the school setting

## Background

An unhealthy diet and lack of physical activity are among the most important risk factors for chronic diseases like cardiovascular diseases, different types of cancers and diabetes in Sweden and globally [1]. In addition, these health behaviours increase the risk of overweight and obesity from early childhood and throughout the life course [2]. More than half of the adult population in most high-income countries now is overweight or obese [3]. Previous studies from Sweden and other high-income countries have shown that children of parents with lower educational attainment [4, 5] and non-Nordic origin [6, 7] have a higher consumption of unhealthy foods and also higher levels of obesity [8, 9] than children of parents with higher educational attainment and who are Swedish-born. There is consistently a 2–3 fold lower prevalence of childhood overweight and obesity in areas with higher socioeconomic status (i.e. income and education) compared to disadvantaged areas [10], which is also found among adults [11]. Given this, there is a need for interventions that start at an early age and target the whole family. Systematic reviews have concluded that due to accessibility to reach nearly all children in a given community, schools are an ideal setting for the delivery of health programs, particularly for children 6–12 years of age [2, 12]. Effective school-based programs are characterised by active parental involvement, especially for younger children [13, 14]. Parents are key in shaping the food and meal environment, providing and reinforcing opportunities for physical activity, model healthy habits, and establish social and cultural norms that promote health for their children [15–17].

### Determinants of implementation and implementation strategies

In order for evidence-based programs to affect population health, they have to be implemented with high fidelity at scale and sustained over time, which has been difficult to achieve [18], especially for more complex multi-level programs. One reason for this is that context-specific determinants of successful implementation are often not identified and used to inform the development of tailored implementation strategies [19]. The Consolidated Framework for Implementation Research (CFIR) is a useful framework that can be used by implementation researchers with community partners to identify context-specific determinants potentially influencing implementation. It includes 39 constructs across five domains; the intervention itself, the inner setting, the outer setting, characteristics of providers, and the implementation process [20]. Three of the 39 constructs have repeatedly been shown to relate to implementation success, namely stakeholders’ perception of the advantage of the intervention relative to other programs, the tension for change as perceived by stakeholders, and if clients’ needs are prioritised by the organisation and resources are present [21]. Other important constructs are relative priority and planning [21]. To accommodate the multi-level nature of interventions including both children and parents, a sixth domain in the CFIR has been proposed called “characteristics of intervention recipients” [21]. A construct that has received increasing attention in the inner setting as an important factor for implementation success is the construct “Readiness for Implementation”, also called organizational readiness [22]. Organizational readiness is a determinant of successful adoption which is necessary for implementers to persist toward fidelity.

Developing implementation strategies that are tailored to context-specific implementation determinants is more likely to improve fidelity to the intervention than no strategies or simple dissemination of guidelines [23]. Determinants of implementation at both individual (provider and service recipient) and organisational levels should therefore be carefully identified as a first step, preferably in collaboration with key stakeholders [24]. However, it is not yet clear how best to tailor strategies and therefore not clear what the magnitude of the effect is that tailored implementation strategies have on both implementation and service recipient outcomes [24]. Assessment of fidelity to the intervention components is one way of evaluating the effectiveness of tailored implementation strategies.

The Expert Recommendations for Implementing Change (ERIC) Project has yielded a significant contribution to establish a common language and taxonomy of 73 unique implementation strategies in health [25]. Cook et al. adapted the ERIC taxonomy for use in the school context, with 75 unique implementation strategies from which to choose and tailor strategies to context-specific barriers, the SISTER taxonomy [26]. A recent study by Lyon et al. including 200 school-based consultants who support social, emotional, and mental health services found that the five strategies rated as most important were: (a) Conduct ongoing training, (b) Make training dynamic, (c) Provide ongoing consultation/coaching, (d) Monitor the progress of the implementation effort, and (e) Improve implementers’ buy-in. The five strategies rated as most feasible were (a) Make training dynamic, (b) Distribute educational materials, (c) Remind school personnel, (d) Facilitation/problem solving, and (e) Capture and share local knowledge. Using these types of implementation strategies in isolation as standalone approaches is not advised as there are numerous determinants influencing successful implementation. Rather, what is needed is a bundle of strategies that target different barriers within a given context to achieve high fidelity to and effectiveness of school-based interventions. Reporting on fidelity to the implementation strategies is equally as important to understand how and why successful implementation of the intervention comes about [27]. Strategies should be clearly described according to features such as a) the actor; b) the action; c) the action target; d) temporality; e) dose; f) implementation outcome affected; and g) the justification for use [28].

### The Healthy School Start program

Development of the Healthy School Start program (HSS) began in 2010 and to date the program has been evaluated in three waves. It is based on Social Cognitive Theory with parental self-efficacy, role modelling, and observational learning as central constructs and mediators of child behaviour change [29]. The program is designed to run in compulsory pre-school class or grade 1 (child age 5–7 years) and is universal (reaches all children). It can be characterised as a structured work routine to fulfil the requirements in the curriculum for teachers to teach about health. It is also fully in line with the Swedish national guidelines for school health care concerning health promotion and prevention of overweight and obesity [30]. Despite the existence of these guidelines, no specific evidence-based practice is recommended. This results in inconsistencies in practice and negative parental responses are often encountered by school nurses when it comes to the issue of child weight development [31].

The program targets parents of children during a developmental period in which health-related behaviours are still very much under the influence of parents [29]. The program is delivered by teachers, school nurses and primary health care staff, and involves four core components: 1) A health information brochure to parents; 2) Motivational interviewing (MI) sessions with parents performed by the school nurse; 3) Classroom activities performed by teachers with home assignments to be completed by children together with their parents; and 4) a web-based self-test of type 2 diabetes (T2D) risk for parents with a recommendation to seek medical advice in primary health care, if needed. These four components were designed to be complementary and mutually reinforcing as emphasised by Gittelsohn [32], who summarised challenges and lessons learnt from multi-level and multi-component interventions to prevent and reduce childhood obesity in different countries. In previous trials of the HSS program, the following implementation strategies used were used based on experience and the literature: 1) Obtain formal commitments, a written agreement with each school specifying school and researcher obligations; 2) Distribution of educational materials like the health brochure, information on the project website and video instructions for teachers; 3) Ongoing training, MI training for school nurses; and 4) Prepare families to be active participants through a kick-off meeting for school staff and parents together.

The program has been evaluated in schools with mixed socioeconomy [33] and in disadvantaged areas [34] in the greater Stockholm area. Fidelity to the intervention components was high for the MI component performed by external MI counsellors in the first two trials, and the classroom component performed by teachers. In the first trial [33] we found significant beneficial effects on dietary habits (higher consumption of fruit and vegetables and lower consumption of unhealthy foods and drinks in the intervention group relative to control). In the second trial [34] we also found a significantly lower BMI z-score in children with obesity at baseline compared to control. In an attempt to increase the involvement of parents in the program, a validated short non-invasive tool to identify individuals at high risk for type 2 diabetes (FINDRISC) [35] was added to the third trial. Undiagnosed diabetes and prediabetes are common in Sweden [36]. If detected early, lifestyle modification can reverse this condition [37] and potentially have beneficial effects on the whole family. In addition, an increased emphasis was placed on parental feeding practices and child physical activity, and the MI was conducted by trained school nurses in the third trial [29]. Results from the third trial running from 2017 to 2019 are in line with the previous studies (manuscript submitted).

During previous evaluations of the HSS program the following implementation barriers were encountered: low priority given to health promotion in schools relative to achievement of learning outcomes [38], lack of positive leadership [39], lack of preparation time [40], the need for clear communication and collaboration between teachers and parents, especially regarding the children’s home assignments [41], and difficulty to engage parents in low-income areas due to stressful everyday life and lack of knowledge and parenting skills [16, 39]. Furthermore, it was found that commitment among staff is important for high intervention fidelity [38]. Addressing these barriers could be achieved through the establishment of an implementation team [38], and by receiving resources and support from external partners such as public health teams [42, 43]. Ultimately, there are numerous barriers that impact the successful implementation of school-based health programs like the HSS that warrant tailored approaches that target these determinants to achieve high fidelity.

The overarching purpose of IMPROVE is to conduct a hybrid type 3 evaluation design to test the effects of bundled implementation strategies on the intervention fidelity of the HSS program while simultaneously monitoring effects on health outcomes of children and parents. There are two primary aims of IMPROVE: 1) To assess the comparative effectiveness of two bundles of implementation strategies (Basic and Enhanced) on the fidelity to the HSS program components; and 2) to monitor effects of the HSS program on child (diet and weight status) and parent outcomes (feeding practices and T2D risk). This study protocol follows the SPIRIT guideline [44] (Additional file 1).

### Specific aims and hypothesis

The hypothesis is that the use of tailored implementation strategies with a focus on facilitation, monitoring, and feedback will lead to significantly better fidelity to the HSS intervention and to sustained effects on child and parent health outcomes. This study will be guided by the following research questions (question 1 has already been addressed):
What context-specific implementation determinants do stakeholders from municipalities in Sweden identify with regard to the implementation of the HSS program?Which of two bundles of tailored implementation strategies is most effective at improving fidelity, acceptability, appropriateness, feasibility, and organisational readiness to implement the HSS program?Does implementation of the HSS program at scale reduce social disparities in the proportion of children with overweight and obesity, and T2D risk among adults?What external implementation support will be needed to facilitate the sustainment of the program after the end of the study?

## Methods

### Study design

A hybrid type 3 cluster-randomized implementation effectiveness trial with 2 parallel arms (Basic and Enhanced) will be conducted (Fig. 1). Hybrid type 3 trials experimentally test the effects of implementation strategies on implementation outcomes while also gathering data on the effects on service recipient outcomes [45]. The primary dependent variable will be fidelity to the HSS (implementation outcome). Using a hybrid type 3 design is advantageous when (a) there is a high momentum and mandate for implementation despite a somewhat limited evidence base, (b) effects are suspected to be vulnerable to a “voltage drop” when scaling up into routine practice, and c) the implementation strategies being tested are reasonably feasible in context [45]. Figure 1 shows the program theory of IMPROVE using the evaluation model by Proctor et al. [46].

**Fig. 1 Fig1:**
[figure not shown]
Program theory of IMPROVE

### Setting of the study

Eight municipalities in the Stockholm Region, Sweden, which had previously shown interest in the HSS program were contacted during the fall of 2020 to inquire about their willingness to take part in the IMPROVE study. Information meetings were held between the research team and key personnel such as central administrators and coordinators of school health care to create interest by explaining the rationale and background to the HSS. Two municipalities finally accepted this invitation after discussing it with their education administration. These municipalities had 110,000 and 50,000 inhabitants respectively, with mixed socioeconomy.

### Implementation strategies used during the planning stage

Implementation strategies to be performed by the research team and school staff are named in this protocol according to the SISTER taxonomy specific for the school context [26]. Expert implementation support was offered as well as free training of school nurses in MI (at a value of ca. 1000 Euro per nurse) to incentivise participation in the study (implementation strategy 51: Improve implementer’s buy-in). The participating municipalities signed a memorandum of understanding with the research team that acknowledges their commitment to the study, and describes the role of each partner (strategy 31: Obtain formal commitments). All public primary schools in the municipalities with preschool classes were invited to participate in the study (*n* = 38). Online information meetings with all groups of involved school personnel were held in the spring of 2021 during which they were introduced by the research team to the HSS and the IMPROVE study and given the opportunity to ask questions. After this, school principals were formally asked if their school wanted to participate, which eight of them declined, mainly due to issues related to the covid-19 pandemic. Before the start of the study all involved school personnel will be asked to consent to be included in the study.

### Eligibility of families, inclusion criteria

All children starting pre-school class (5–7 years of age) during the school year 2021/22 and 2022/23 and their parents/guardians are eligible for the study. The HSS program will be presented to parents as part of ordinary school routines, which means that all children and parents will take part in the program and be invited to participate in the study. At the first meeting in school with the class teacher, parents will receive oral and written information about the HSS and the IMPROVE study and a consent form. They will be informed that all families will be exposed to the HSS as part of school routines, but that participation in the IMPROVE study is voluntary and that no personal information or identities will be disclosed.

### Randomisation and blinding

Within each municipality, schools will be randomised 1:1 to group 1 (Basic: bundle 1) or group 2 (Enhanced: bundle 1 + 2) using a computer-generated assignment by an independent statistician after baseline measurement has been conducted in September 2021. It is not possible to blind school staff and the research team to allocation, but parents and children will not get this information. The CONSORT flow diagram with the number of schools and children is shown in Fig. 2.

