##### Parental feeding practices

Parental feeding practices, including modelling, will be measured using the Comprehensive Feeding Practices Questionnaire (CFPQ) developed by Musher-Eizenman, covering both positive and negative practices, and validated in a middle-income US sample [64]. We will use the Swedish short version with 36 items. The questionnaire will assess the parental feeding practices of involvement, environment, food restriction for weight control, restriction for health reasons, encouragement of balance, pressure to eat, monitoring, emotion regulation, food as a reward, and modelling. The parents are asked to answer the questionnaire online at three timepoints, at baseline, at the end of the school year, and 12 months after that (Table 5).

**Table 5 Tab5:** Outcome, moderators, and time of data collection

Indicator	Time of data collection			
	2021	2022	2023	2024
School characteristics	June			
Parents’ demographic data Fidelity to HSS components	October (C1)	October (C2) June (C1)	June (C2)	
Acceptability	September	June	June	June
Appropriateness	September	June	June	June
Feasibility	September	June	June	June
Organisational readiness	September	June	June	June
Fidelity to implementation strategies		May	May	May
Child height and weight	December (C1)	December (C2)	December (C1)	December (C2)
Child diet	October (C1)	June (C1) October (C2)	June (C1 + C2)	June (C2)
Parents’ T2D risk	October (C1)	June (C1) October (C2)	June (C1 + C2)	June (C2)
Parental feeding practices	October (C1)	June (C1) October (C2)	June (C1 + C2)	June (C2)

*C* cohort of children

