### Data management and statistical analysis

Data collection will be performed in a secure web platform Research Electronic Data Capture (REDCap) for building and managing online databases and surveys [67, 68]. All data will be stored electronically in password-protected folders on a secure data server with systematic back-up routines at Karolinska Institutet to avoid unauthorized access. Folders containing raw data will be stored separately from the data being used in the analysis. Access to data will be restricted to the research personnel working directly with data entry or analyses. A detailed statistical analysis plan will be developed in collaboration with an academic statistician prior to the start of data analysis.

Baseline characteristics at both school and individual level will be cross-tabulated for group 1 and 2 to check for balance and to provide an overview of the study population. Continuous and normally distributed variables will be represented as mean, standard deviation and range. Non-normally distributed variables will be represented as median and interquartile ranges, and categorical variables will be presented as frequencies and percentages in each category.

Assessment of the primary outcomes adherence score and responsiveness score after 12 and 24 months will be performed on the individual level. Between-group effects in the adherence score (0–4) will be analyzed using ordinal logistic regression. Between-group effects in the responsiveness score (4-20) will be analyzed using mixed linear regression. The following factors will be explored as potential moderators of fidelity to intervention: school size, fidelity to implementation strategies, baseline organisational readiness, parent educational level and country of birth.

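### Allocation of the 30 schools is restricted by municipality only, so school size and baseline readiness are left to chance although both can be balanced beforehand

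*Protocol article*

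**What the plan says.** The abstract gives the number of clusters: "Thirty schools in two municipalities will participate in the study reaching about 1400 families per school year". The Randomisation and blinding section fixes the allocation: "Within each municipality, schools will be randomised 1:1 to group 1 (Basic: bundle 1) or group 2 (Enhanced: bundle 1 + 2", done "using a computer-generated assignment by an independent statistician after baseline measurement has been conducted in September 2021". Municipality is the only restriction named. One randomisation after one baseline implies that all schools are known when the list is drawn.

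Table 5 has, in its 2021 column, the entries "School characteristics June" and "Organisational readiness September". Both therefore precede allocation.

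The article treats these variables as relevant to the primary outcome. The Background section on implementation determinants describes organisational readiness as something implementers need if they are to keep working toward fidelity. The statistical analysis section lists school size and baseline readiness among the potential moderators of fidelity. The setting is described as two municipalities "with mixed socioeconomy".

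After allocation, baseline characteristics "will be cross-tabulated for group 1 and 2 to check for balance". The abstract says that covariates will be considered where needed. The article fixes no adjustment set for the two primary outcomes and defers detail to a statistical analysis plan.

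**The concern.** With about 15 schools per arm, randomisation within two municipalities gives only loose control over other school-level variables. A single draw can put the larger or the less ready schools mostly in one arm. The article says these variables may bear on fidelity, and it has them before the draw, but the stated scheme does not use them.

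At stake are the precision of the comparison and how readily readers accept it. A visible imbalance in readiness between Basic and Enhanced would raise the question of whether a fidelity difference reflects the strategies or the schools. A later analysis plan can adjust for such an imbalance, but it cannot change an allocation already made. The choice therefore belongs in the protocol.

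**Working it through.** **The plan's own figure.** The article gives no figure for covariate balance. Its power figure for the responsiveness score can be reproduced and supplies the outcome scale. Inputs from the sample size section: 400 parents per group, SD 8, differences 0.8, 1.6 and 3.2. Assumed: two-sided alpha 0.05, no clustering.

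- SE = 8 × sqrt(2/400) = 0.566
- Power = Φ(difference/0.566 − 1.96) = 0.293, 0.807 and 0.9999, against 0.29, 0.81 and 0.99 stated. It reproduces.

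**Chance imbalance under the stated scheme.** Input: 30 schools at 1:1, so about 15 per arm. For a standardised school-level covariate:

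- SD of the arm difference = sqrt(1/15 + 1/15) = sqrt(2/15) = 0.365
- P(difference above 0.5 SD, either direction) = P(|Z| > 0.5/0.365) = 0.171
- P(above 0.25 SD) = P(|Z| > 0.25/0.365) = 0.494
- For at least one of k independent covariates, 1 − (1 − p)^k:

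| Threshold | One | Any of two | Any of three |
|---|---|---|---|
| 0.5 SD | 17% | 31% | 43% |
| 0.25 SD | 49% | 74% | 87% |

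The split of schools between municipalities is not given. Simulated stratified randomisation with assumed splits of 20/10, 21/9 and 18/12, and covariates either uncorrelated or correlated 0.3, gave much the same:

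- One covariate: about 18% above 0.5 SD and 50–51% above 0.25 SD.
- Any of three: 42–44% above 0.5 SD and 87–88% above 0.25 SD.

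**Effect on the estimate, as illustration only.** Assume one covariate that explains 40% of between-school variance. Assume ICCs of 0.02, 0.05 and 0.10. The article gives neither quantity.

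- Shift of the unadjusted estimate from a 0.5 SD imbalance = 0.5 × sqrt(0.4 × ICC) = 0.045, 0.071 and 0.100 SD
- SE of a clustered comparison, 400 parents in 15 schools per arm = sqrt((2/400) × (1 + (400/15 − 1) × ICC)) = 0.087, 0.107 and 0.134 SD
- Shift as a share of one SE = 0.51, 0.66 and 0.75

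**Precision at stake, same assumptions.** The covariate's contribution to the variance of the unadjusted difference is 0.4 × ICC × 2/15 = 0.0011, 0.0027 and 0.0053. The total variances are 0.0076, 0.0114 and 0.0178, so the shares are 14%, 23% and 30%. Removing that part entirely would cut the SE by about 7%, 12% and 16% (1 − sqrt(1 − share)). This is an upper limit for such a covariate, whether it is handled by design, by analysis or by both.

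**Under constrained randomisation.** With an assumed 20/10 split, three covariates, and a draw from the best-balanced 10% of candidate allocations, the simulated chance that any of the three differs by more than 0.5 SD fell from about 44% to about 0%. For more than 0.25 SD it fell from about 88% to about 8%.

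**The case against.** The strongest reply is that nothing here is an error. Stratified 1:1 allocation by an independent statistician after baseline is valid and unbiased in expectation, and leaving out a refinement contradicts nothing in the article. That stands. It limits the point to an improvement.

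Several stronger readings are tempting, and the documents do not support them.

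- *A reader might infer that the estimate will be biased.* It will not be. The illustrative shift is half to three quarters of one clustered SE and can go in either direction. It is ordinary between-school variation, already carried by a model that accounts for clustering.
- *A reader might infer that a large imbalance is likely.* At 0.5 SD it is not: 17% for one covariate, and below one half for three. Only at 0.25 SD, across several covariates, is imbalance the expected result.
- *A reader might attach the illustrative shift to the 43%.* The two do not combine. Three independent covariates at 40% each would explain 120% of between-school variance. A single strong covariate carries the 17%.
- *A reader might express the shift as a share of a target effect.* The sample size section names no target. Against 1.6 points at SD 8 (0.2 SD) the shares would be 22%, 35% and 50%. At the section's alternative SD of 4 the same 1.6 points is 0.4 SD and the shares halve.
- *A reader might infer that nothing can be done after allocation.* Adjustment recovers part of the loss, and an analysis plan not shown may prespecify it.
- *A reader might assume that a school-level socioeconomic measure is at hand.* The contents of the June school characteristics are not stated, and Table 5 places parents' demographic data in October 2021, after the September baseline.

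What remains is that the allocation is a protocol decision and that relevant data precede it. Thirty clusters also leave room for only a few adjustment covariates, so balance obtained by design is worth having.

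**Conclusion.** The point holds as an inexpensive improvement to a valid design. Restricting only on municipality leaves about a one in six chance of an imbalance above 0.5 SD in any given school-level covariate, and about 43% for at least one of three independent covariates. Above 0.25 SD the chances are about 50% and 88%. These probabilities need only about 15 schools per arm and approximately normal covariates, and they change little with the assumed municipality split or modest correlation. The consequence is lost precision and a comparison that is harder to defend. Its size on the outcome scale depends on an ICC and a share of variance explained that the article does not give, so those figures are illustrative.

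**What to change.** In the Randomisation and blinding section, state that the independent statistician will use covariate-constrained randomisation within municipality:

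1. Balance school size and mean baseline organisational readiness. Add a school-level socioeconomic measure only if the June 2021 school characteristics contain one.
2. Define the balance criterion before allocation, and draw the final allocation at random from a sufficiently large set of acceptable ones.
3. Keep the balancing variables in the models for both primary outcomes.

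The cost is some time from a statistician already engaged and a sentence or two of text. There are two small downsides. The primary models are committed to a few school-level covariates with only 30 clusters. Readiness, which comes from individual staff questionnaires, must also be returned and scored for every school between the September baseline and the draw. If the allocation has already been made, only prespecified adjustment for these variables remains open.
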